### Outcome measures

The methods of participant assessment have been carefully considered as assessments are taking place in people's homes. All study measures will be assessed at baseline, 6, 12, 18 and 24 months.

The main outcome measure of this study is long term adherence to physical activity. Adherence will be measured using exercise diaries completed over the 2 year study period, a continuous measure. Exercise diaries have been found to be both reliable and valid [28]. Participants will be encouraged to record date, type, duration and intensity, using the modified Borg rating of perceived exertion scale (RPE) [29], every time they are physically active. Participants will be encouraged to return the diaries in the supplied prepaid envelope at the end of each month over the study period.

Average monthly adherence rates across the 2 year period will be calculated as follows: number of physical activity sessions reported as a percentage of physical activity sessions prescribed for the month. This is similar to the method described by King [20] to determine adherence rates to different physical activity intensities and formats over a 2 year period. The number of sessions prescribed for the month will be based on the World Health Organisation (WHO) physical activity guidelines [3]. That is, 30 min of moderate intensity physical activity, five or more days per week, a total of 20 or more sessions per month. Thirty minutes can be accumulated in 10 min bouts of physical activity per day. Moderate intensity is defined as a rating of 3 or more on the modified Borg RPE scale.

Secondary outcomes include the Active Australia Survey (AAS), accelerometry, aerobic capacity (2 min step test), quality of life (SF-12v2) and disease biomarkers, that is, waist circumference (cm), waist:hip ratio (WHR), blood pressure (mmHg) and body mass index (BMI, kg/m^2^).

The AAS and accelerometry will be used to validate the data collected from the exercise diaries. These two continuous measures will be collected every 6 months over the 2 year study period.

The AAS has been designed to measure participation in leisure time physical activity and to assess the participant's knowledge of current public health messages about the health benefits of physical activity. It offers a short and reliable set of questions and applies to 1 week preceding the interview, including walking for transport. The AAS has been reported as reliable and of acceptable validity [30,31].

Covering the same time period as the AAS, participants will wear an Actigraph GT1M accelerometer [32] for 7 consecutive days. Accelerometers allow an objective measurement of quantity and intensity of movement and have been found to be reliable and valid [33].

The raw data collected by the accelerometer, counts, will be used to obtain the time spent in different physical activity intensities [34]. We will use the Freedson Combination energy expenditure algorithm to determine the intensity cut-points [32]. This outcome variable will be used to investigate whether participants have reached the WHO physical activity guidelines.

Assessment of aerobic capacity is essential to determine whether the completed physical activity has been intense enough to result in an improvement in cardiovascular fitness. The 2 min step test requires little space and equipment, with large studies finding it both reliable and valid [35]. The 2-minute step test protocol involves determining the number of times in 2 min that a person can step in place raising the knees to a height halfway between the patella (kneecap) and iliac crest (front hip bone), a continuous measurement. Only one successful trial will be administered.

The SF-12v2 is a general health status questionnaire which has a 12-item scale producing eight separate sub-scales (physical functioning, physical role functioning, emotional role functioning, social functioning, bodily pain, mental health, vitality and general health perceptions) to assess quality of life [36]. It takes the participant less than 2 min to complete the tool and is a quasi-continuous measurement.

Waist circumference and hip circumference will be measured in centimetres using a tape measure. Blood pressure levels will be obtained using a mercury sphygmomanometer on the right arm of seated subjects. Both measures will be taken twice and then the average will be recorded. BMI (kg/m^2^) will be recorded using a portable set of scales and a stadiometer.

Sociodemographic information will also be collected with questions regarding participant's education level, relationship status, current employment status and the presence of any chronic diseases.

Qualitative data will be collected at the end of the intervention period in both the group exercise and physiotherapy-led home based physical activity programs. Telephone administered semi-structured interviews will be conducted with a sub-sample of both the group and home based interventions. Focus groups will also be conducted, with sub-samples of attendees and non-attendees for both the home based and group interventions. These approaches together with the qualitative data should provide improved data collection, guiding future physical activity programs.

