### Intervention

(i) Home-based intervention

Assessments for the home based program in this study will be conducted in participant's homes eliminating a number of barriers to physical activity adoption as discussed earlier [24]. Participants will be encouraged to invite a support person to attend during their initial assessment. After baseline measures are completed motivational interviewing will be used to devise an individual physical activity program [25]. A physiotherapist will discuss type, frequency, intensity, duration, benefits, barriers, goals, self-monitoring and progression of physical activity, aiming to achieve 30 min of moderate intensity physical activity most days of the week. Participants will be contacted by a physiotherapist via phone providing advice and support 2 weeks after the initial assessment and then monthly over a 6 month period, a total of approximately 6 phone calls.

(ii) Usual Care

Participants randomised to usual care will be visited by the physiotherapist in their homes. Baseline measures for the study will be completed giving participants an indication of their fitness and health status. Participants will receive two brochures 'An active way to better health. National Physical Activity Guidelines for Adults' and 'Dietary Guidelines for Australian Adults' from the Department of Health and Ageing [26,27]. They will not receive any other advice or support for increasing exercise or physical activity levels.

(iii) Group exercise program

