## Discussion

Over a 2 year period the 'Physical Activity at Home' study will test the effectiveness, in terms of long term physical activity adherence, health benefits and cost, of a physiotherapy-led home based physical activity program. Specifically it will target middle aged adults who are less likely to adopt and maintain physical activity, as they do not access the currently available community group exercise programs. With few studies reporting on the long term adherence to physical activity post intervention and no known studies reporting on targeted physical activity interventions for those not interested in group or centre based programs, if this program is successful it could allow more individuals to increase their physical activity levels towards that needed to achieve the associated health benefits.

One of the strengths of this trial is that the inclusion criteria are broad proposing that there is some benefit from physical activity for almost everyone [42]. The recruitment method also attempts to minimize self-selection and recruitment of highly motivated volunteers by using the electoral roll, allowing a more representative sample [24]. Phone coverage is widespread in Australia therefore recruitment and providing the home based intervention via this method should also limit selection bias. All measurements will be performed by the same person and the sample size to be recruited should provide adequate statistical power to detect a significant difference in the main outcome measure.

A limitation of this study is the lack of randomisation to the group and home based interventions limiting the ability to attribute outcomes to treatment for all three groups. There is also a lack of blinding, as the principal researcher will be conducting all assessments and providing the home based intervention. Another possible limitation is the type of personnel conducting the interventions is not standardised, that is, a physiotherapist as compared to a fitness instructor.

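### The primary outcome is an unblinded self-report diary and only the home arm is coached on intensity and self-monitoring, so the diary should be checked against the accelerometer separately by arm

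*Protocol article*

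**What the plan says.** **Primary outcome (Outcome measures).** The main outcome is long-term adherence: "Adherence will be measured using exercise diaries completed over the 2 year study period, a continuous measure". It is calculated as the "number of physical activity sessions reported as a percentage of physical activity sessions prescribed for the month", and the prescribed number is "a total of 20 or more sessions per month". The intensity threshold is also the participant's own judgement: "Moderate intensity is defined as a rating of 3 or more on the modified Borg RPE scale". Diaries are asked of participants in general and posted back monthly.

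**What differs between the randomised arms (Intervention).** In the home arm a physiotherapist discusses, among other things, intensity and "benefits, barriers, goals, self-monitoring and progression of physical activity", followed by about six calls over 6 months. Usual care receives two brochures, and "They will not receive any other advice or support for increasing exercise or physical activity levels".

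**Blinding (Discussion).** "There is also a lack of blinding, as the principal researcher will be conducting all assessments and providing the home based intervention". The limitations listed there do not mention differential reporting in the primary outcome.

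**Accelerometry (Outcome measures).** It is worn for 7 days at baseline, 6, 12, 18 and 24 months, over the same period as the AAS. It has three stated roles. It is a listed secondary outcome, it is used to judge whether the WHO guidelines are reached, and "The AAS and accelerometry will be used to validate the data collected from the exercise diaries".

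**The concern.** The home program can act on the diary by two routes. It can change how much activity is done, which is the effect of interest. It can also change how completely activity is written down and how readily effort is rated 3 or more. Discussing self-monitoring and intensity, with repeated calls, bears on the second route in one randomised arm only.

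Neither analysis safeguard in the article removes such a difference. Intention-to-treat preserves the randomised groups, and baseline adjustment handles differences present at entry. A recording difference caused by the intervention arises after both.

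At stake is the meaning of a positive result: more activity, or partly more recording. The trial already holds a measure that does not depend on participants' reporting. However, the validation is stated only in general terms, and a general validation does not answer this question.

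**Working it through.** **Inputs.** From Sample size: difference 20 points, SD 35, dropout 25%, power 0.8. From Statistical methods: significance level 0.05, with no sidedness stated, so two-sided is assumed. From Outcome measures: 20 sessions per month. The amount of over-recording is not in the document and is varied below.

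**1. The plan's own figure.** n per arm = 2 × [35 × (1.960 + 0.842) / 20]² = 48.07, and 48.07 / 0.75 = 64.1. The stated 64 is reproduced. (Rounding up to 49 before inflating gives 66.) A one-sided test would give 38, inflated to 51, so two-sided is implied.

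**2. Scale.** One recorded session is 1/20 = 5 points in that month.

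**3. Smallest significant difference.** With 48 completers per arm, SE = 35 × √(2/48) = 7.14. The threshold is 1.96 × 7.14 = 14.0 points, or 14.0/5 = 2.8 sessions per month sustained over 2 years.

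**4. Chance of a false home win.** With no true effect and a recording gap of b points, the chance of a significant result favouring home is Φ(b/SE − 1.96). For b = 5: Φ(0.70 − 1.96) = 10.4%.

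| Extra sessions recorded, home arm only, over 2 years | Points | 48 per arm | 64 per arm (SE 6.19) |
|---|---|---|---|
| none | 0 | 2.5% | 2.5% |
| 1 per month | 5 | 10.4% | 12.5% |
| 2 per month | 10 | 28.8% | 36.6% |
| 3 per month | 15 | 55.6% | 67.9% |
| 4 per month | 20 | 79.9% | 89.8% |

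**5. Gap confined to the 6 supported months.** One extra session per week is 52/12 = 4.33 per month, and 4.33/20 = 21.7 points while it lasts. Averaged over 2 years this is 21.7 × 6/24 = 5.4 points, giving Φ(5.4/7.14 − 1.96), about 11%. Half a session per week gives 10.8 × 6/24 = 2.7 points, about 6%.

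Steps 3 to 5 use a simple comparison of two means with the plan's SD. The planned repeated measures ANCOVA would have a different SE.

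**6. Why pooling does not help.** Suppose home over-records by g and usual care by nothing. With equal arms the pooled mean gap is g/2. That cannot be told apart from g/2 in both arms, which would not bias the comparison at all. Only the difference in gap between arms separates the two cases. Agreement with the AAS does not settle it, because the AAS is also reported by the same unblinded participants.

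**The case against.** Several parts of the case on the other side stand.

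- A reader might infer that the accelerometer serves only to validate the diary. The article does not support that: accelerometry is also a named secondary outcome and is used to judge guideline attainment, so an objective comparison is foreseen.
- A reader might infer that a home effect would be nothing but reporting. That is a possibility, not something the document shows. Self-monitoring is described as discussed. Training in completing the diary or rating exertion is not described, and every participant is asked for the same entries. Talking about intensity could also make ratings stricter, so even the direction is assumed.
- The assessor's double role does not reach the primary outcome directly, because participants fill in the diaries and post them.
- The article cites support for diary reliability and validity. That source cannot be checked here, and validity in general is a different matter from equal reporting in a coached and an uncoached arm.
- One extra session per week need not exceed the 20-point design difference. The 21.7 figure uses 4.33 weeks per month, while 20 sessions is five per week over four weeks. On that scale it is 4/20 = 20 points, equal to the target.
- If over-recording stops when the calls stop, the 2.7 to 5.4 points are well below the 14.0 needed for significance.
- How the validation is analysed may be set out in a full protocol or analysis plan that is not shown. Its absence from the article is therefore not a fault in itself.

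What remains is a choice fixed in the article: the headline conclusion rests on the measure most exposed to a reporting effect of the intervention, and the validation is described without reference to arm.

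**Conclusion.** The point holds as a moderate weakness of the randomised comparison. The primary outcome is an unblinded self-report with self-rated intensity, and coaching that bears on recording goes to one arm only. A home advantage could therefore partly be a recording difference.

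Under assumptions that the document neither supports nor excludes, the chance of a false home win rises from 2.5% to about 10% for one extra session per month throughout, or about 11% for one per week in the supported period only. A gap expected to be 2.8 sessions per month over 2 years sits at the significance threshold, so it would give a significant result about half the time with no true effect. These figures rest on SD 35, 48 completers per arm, a two-sided 0.05 level and no true effect.

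The stronger conclusion that accelerometry should become co-primary or a formal gate does not follow. The sample size is based on diary adherence and gives no accelerometer SD or difference. Seven days every 6 months also cannot stand in for a continuous 2-year record.

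**What to change.** Keep the diary as the primary outcome. In Outcome measures, replace the general validation statement with the following:

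- At 6, 12, 18 and 24 months, calculate for each participant the diary minutes of at least moderate intensity minus the accelerometer minutes of moderate-to-vigorous activity over the same 7 days. The diary already asks for date, duration and intensity, so the days can be matched.
- Summarise this gap by arm, and report the between-arm difference with its confidence interval beside the primary result. The gap need not be zero in either arm, because the two instruments define intensity differently. The between-arm difference is what matters.
- Beside it, report the baseline-adjusted between-arm accelerometer difference at 12 and 24 months.
- Describe a diary difference without accelerometer support as a difference in reported adherence.

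The 6-month comparison covers the end of the supported period, and the later ones show whether any gap persists.

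The cost is some extra analysis on data already collected. The limits are one sampled week per visit and activity types that accelerometers may miss. If the arms favour different activities, the gap could differ for that reason, and the activity type recorded in the diary should be examined before it is read as over-recording.

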4. Those that commence the home based physical activity program are more likely to continue with an increase in physical activity in the long term, as compared to a group based program.

5. A home based approach to increasing physical activity with minimal support is more cost effective than a group based intervention, taking into consideration long term physical activity adherence.

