Participants in the group based program will attend the YMCA for their baseline measures. Baseline measures will be conducted by the same physiotherapist as the home based interventions. Participants will then have a choice of times for the group based exercise program which will be during business hours replicating similar programs and times offered in this community setting. These sessions will be run by a YMCA fitness instructor at the YMCA once a week, for 60 min, over 6 months. The exercise program will involve upper and lower body strengthening exercises, gross motor skill training and aerobic fitness training. The exercise specifics will be at the discretion of the YMCA fitness instructor, with no involvement from the physiotherapist, aiming to mimic 'usual practice'. Participants will be encouraged to increase their physical activity slowly and gradually in whichever way they prefer outside of the group sessions by the YMCA fitness instructors, aiming to achieve 30 min of moderate intensity physical activity most days of the week. An individual home based exercise program will not specifically be designed for this group.

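### In the subsidiary home-versus-group comparison, the session-count adherence score gives a 60-minute class no credit beyond 30 minutes, which favours home by up to 20 points in months 1-6 and up to 5 over 24 months

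*Protocol article*

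**What the plan says.** Under Outcome measures, the Protocol article defines the primary outcome, adherence from exercise diaries, as the "number of physical activity sessions reported as a percentage of physical activity sessions prescribed for the month". The number prescribed is the same for every arm: "30 min of moderate intensity physical activity, five or more days per week, a total of 20 or more sessions per month". Short bouts may be combined: "Thirty minutes can be accumulated in 10 min bouts of physical activity per day". No rule credits time above 30 minutes. The diary does hold the length of each session ("Participants will be encouraged to record date, type, duration and intensity"), but the formula does not use it to give longer sessions more weight. The period covered is the whole study: "Average monthly adherence rates across the 2 year period will be calculated as follows".

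Under Intervention, the home program is individually devised, "aiming to achieve 30 min of moderate intensity physical activity most days of the week". The group program is a class: "These sessions will be run by a YMCA fitness instructor at the YMCA once a week, for 60 min, over 6 months". Group members are also encouraged to be active outside the class, with the same overall aim as the home arm.

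Hypothesis 4 in the Background compares home with group: "Those that commence the home based physical activity program are more likely to continue with an increase in physical activity in the long term". Other analyses describes the comparison with the group program as subsidiary and gives it the same ANCOVA as the randomised comparison. Sample size takes its 20-point difference from a home-versus-group contrast in a cited study.

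**The concern.** Hypothesis 4 concerns an increase in physical activity, whereas the outcome counts sessions. The two programs deliver activity in blocks of different length. Sixty minutes at moderate intensity is twice the 30-minute unit behind the target, yet a 60-minute class is one session on one day, so it counts once under either a session count or a day count. The same minutes as two 30-minute home sessions on separate days count twice.

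Home could therefore score higher than group when both arms do the same amount of activity, and the direction favours the trial's own hypothesis. The Discussion acknowledges the lack of randomisation to group, the lack of blinding and the different personnel, but not this feature of the scoring.

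**Working it through.** **Inputs.** From Outcome measures: target 20 sessions a month, each of 30 min; 5 sessions a week equated with 20 a month, so 4 weeks a month. From Intervention: class 1 x 60 min a week for 6 months. From Sample size: difference 20 points, SD 35, power 0.8, dropout 25%, 64 per group. From Statistical methods: significance level 0.05, taken as two-sided (assumption). Assumed: class attendance of 100%, 75% or 50%; all 60 class minutes at RPE 3 or more; home activity in 30-minute sessions on separate days; other activity equal.

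**1. The plan's sample size.** n = 2 x [35 x (1.960 + 0.842)/20]^2 = 48.07 completers per group; 48.07/0.75 = 64.1. The stated 64 is reproduced and is not in dispute. It implies 0.75 x 64 = 48 completers per group.

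**2. Class minutes only, one month.**
- Group: 4 classes, 4/20 = 20%.
- Home: the same 240 min as 30-minute sessions, 240/30 = 8 sessions, 8/20 = 40%.
- Gap: 20 points.

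**3. With activity outside class, 150 min a week in both arms.**
- Group: class plus three 30-minute sessions, 4 x 4 = 16 sessions, 16/20 = 80%.
- Home: five 30-minute sessions, 5 x 4 = 20 sessions, 20/20 = 100%.
- Gap: still 20 points, but the ratio is 0.8, not one half.

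**4. Dilution.** Classes run in 6 of 24 months, so the averaged gap is (20 x attendance) x 6/24.

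**5. Chance of p < 0.05 with equal minutes.** Standard error = 35 x sqrt(2/48) = 7.14 points. With z = gap/7.14, the probability is Phi(z - 1.96) + Phi(-z - 1.96).

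| Attendance | Gap, months 1-6 | Probability | Gap, 24-month average | Probability |
|---|---|---|---|---|
| 100% | 20 | 0.80 | 5 | 0.11 |
| 75% | 15 | 0.56 | 3.75 | 0.08 |
| 50% | 10 | 0.29 | 2.5 | 0.06 |

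The nominal level is 0.05. The SD of 35 is the planning value, used throughout; a smaller SD for the 24-month average would raise the probabilities in the last column.

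**6. Sensitivity to class intensity.** If m of the 60 class minutes reach RPE 3, the equal-minutes gap in a class month at full attendance is 4 x (m/30 - 1)/20. This gives 20 points at m = 60, 10 points at m = 45 (illustrative) and 0 at m = 30. The gap also shrinks if home participants take longer sessions.

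**7. A minutes-based score.** Minutes/(20 x 30): 60 min a week gives 240/600 = 40% in both arms, and 150 min a week gives 600/600 = 100% in both arms. The gap is zero.

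**The case against.** The strongest reply is that the outcome is adherence to a frequency guideline, and both programs share the aim of 30 minutes on most days. Against that target, one class fills one day of five and is rightly counted once. This stands: the frequency score is legitimate and need not be replaced. What it does not measure is amount of activity, so it cannot alone support a home advantage in amount.

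The article also does not say in words how a 60-minute entry is coded, and the full protocol or analysis plan might. That is fair, but the stated formula and the daily 30-minute rule both lead to a count of one.

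The class mixes strengthening, motor skill and aerobic work at the instructor's discretion, so not every minute need reach RPE 3, and home programs are tailored in duration. Both points stand and make the figures upper bounds.

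Hypothesis 4 is about the long term, classes end at 6 months, and the article specifies no test confined to months 1-6. This stands too: the months 1-6 probabilities illustrate the size of the effect and do not describe a planned test.

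Finally, the Active Australia Survey and accelerometry are there to validate the diaries. They help, but each covers one week every 6 months and neither corrects the diary score.

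**Conclusion.** The point holds for the home-versus-group comparison only, and it is modest. With equal minutes the score favours home by up to 20 points in each month that classes run, and by up to 5 points in the 24-month average (2.5 at 50% attendance). The chance of a significant 24-month result with no difference in minutes is then about 0.06 to 0.11 instead of 0.05. This rests on all class minutes reaching RPE 3 or more, home activity in 30-minute sessions, equal other activity and an SD of 35.

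A reader might infer more than the article supports:
- **That the group arm scores half.** One half applies to class minutes alone; at 150 min a week the scores are 80% and 100%.
- **That the artefact exceeds the design difference.** Using 52/12 = 4.33 weeks a month gives 8.67/20 - 4.33/20 = 21.7 points, but this sets calendar months against a target built on 4 weeks. In consistent units the maximum equals the 20-point design difference.
- **That the main trial result is biased.** The randomised home-versus-usual-care comparison has no built-in difference in session length. The affected comparison is non-randomised and labelled subsidiary.
- **That the gap persists after the program.** Months 7-24 have no class, so nothing is built in unless group members keep up 60-minute sessions.

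**What to change.** Keep the frequency score as the guideline-adherence outcome. For home versus group:

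1. Pre-specify a sensitivity analysis of monthly diary minutes at RPE 3 or more, as a percentage of the minutes the target implies (30 x sessions prescribed).
2. Show months 1-6 and months 7-24 separately.
3. State that a home advantage seen only in session counts will be interpreted as a difference in frequency, not in amount of physical activity.

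Making agreement between the two scores a formal condition for claiming hypothesis 4 would be out of proportion to a bias of 2.5 to 5 points in a subsidiary comparison.

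The cost is some wording and one extra derived variable from durations and intensities already collected, with no new data or participants. The downside is a slightly more cautious reading of hypothesis 4.
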